#### Secondary outcomes

##### Patient-reported outcomes

ACL-RSI scores are summed for a scale from 0 to 100%, with higher scores representing more positive psychological reactions [33]. The Swedish version of the Knee Injury and Osteoarthritis Outcome Score (KOOS) is used to evaluate self-reported knee function [35, 36]. Enjoyment is measured using the Physical Activity Enjoyment Scale (PACES) [37], using an unpublished version translated to Swedish by the authors. Stress is measured using the Swedish version of the Perceived Stress Scale [38, 39]. The patient’s ability to understand and cope with a disease or injury is assessed using the Patient Enablement Instrument [40, 41]. Rehabilitation outcome satisfaction is measured using one unvalidated question (“if you were to spend the rest of your life with your knee function just the way it has been in the last week, would you feel…”) [42]. Rehabilitation motivation is evaluated using three questions adapted from a previous study: “how important is it that you return to your previous activity level?”, “do you think it is possible for you to return to your previous activity level?”, and “how much time and effort are you willing to invest to return to your previous activity level?” [4]. The Tegner Activity Scale [43] is used to assess preinjury, current, and desired future activity level. All questionnaires are available in English.

##### Physical testing

Physical testing is performed in order of difficulty, with activities resembling daily life (single-leg mini squat) being performed first, progressing to more demanding functional tasks (side hop). Tasks are performed with shoes unless otherwise stated. The tasks are described below according to the test batteries in which they will be analyzed.

##### Hop test battery

The hop test battery [6], consisting of two functional tasks (single-leg hop for distance and side hop) performed on both legs, is used to evaluate muscle function. The single-leg hop for distance is done by standing on one leg and performing a maximal jump forward, landing with control on the same leg, and maintaining control for 2–3 s. Failure to maintain landing position results in a disqualified hop and the hop will be repeated. The side hop task is performed by jumping on one leg from side to side over two parallel lines taped 40 cm apart on the floor as many times as possible in 30 s [44]. The number of successful hops without touching the line is recorded. Results are expressed as change in the injured leg, change in the uninjured leg, and limb symmetry index (LSI; LSI = (injured leg/uninjured leg) x100) individually and summed.

##### Postural orientation errors

Postural orientation errors (POEs) are assessed using a test battery consisting of five functional tasks (single-leg mini squat, stair descending, forward lunge, single-leg hop for distance, and side hop) that range from resembling daily life to more demanding activities [45]. The single-leg mini squat [46] is performed without shoes or fingertip support by lifting one leg and lowering the body until the active knee reaches approximately 60° of flexion, then the individual returns to full extension. The stair descending [47] task is performed without shoes by standing on a 30-cm box or raised platform and stepping down from the platform one foot at a time, as though walking down a set of stairs. The forward lunge is performed by standing on a starting line, taking a step forward, and flexing the knee to approximately 90°, then extending to return to the starting position [6]. The single-leg hop for distance and side hop is performed as described above. Tasks are video-recorded from a frontal view for later assessment of the participant’s postural orientation, presented as a total POE score [45].

##### Adherence

Adherence is measured using a weekly self-report survey regarding the number of completed supervised and at-home rehabilitation sessions, the approximate duration of at-home training sessions, and the approximate duration of MOTIFS training during at-home training sessions (final question answered only by the MOTIFS group). Physical therapist attendance records may be requested to confirm the number of completed supervised rehabilitation sessions over the intervention period. Adherence will be compared between groups to determine whether one treatment has higher adherence rates.

One unvalidated self-report question will be posed to participants in the MOTIFS condition in the adherence survey to assess whether they engaged in imagery during the execution of their rehabilitation exercises. The question was adapted from the Vividness of Movement Imagery Questionnaire [48]: “While doing my rehabilitation exercises, the sport-/physical activity-specific image that I create is:” with responses on a 5-point Likert scale ranging from 1 (“as vivid as though I were actually doing it”) to 5 (“not at all vivid”), with an additional option of not applicable if they did not perform imagery during their exercises. This adherence question also provides an indication of whether the physical therapists were prescribing MOTIFS training during physical rehabilitation sessions.

#### Exploratory outcomes

Upon completion of the intervention, a subgroup of approximately 10 participants in each group (or until saturation is reached) will undergo a phenomenological interview about their rehabilitation experience. Phenomenological interviews will also be conducted with physical therapists (approximately *n*=7–10 from each group) to provide insight into potential modifications to be made to the MOTIFS model. These will also provide information regarding how PTs in both the MOTIFS and CaU groups experience planning and executing rehabilitation to treat traumatic knee injury using their assigned intervention. The interviews, consisting of one question regarding their rehabilitation supplemented by probing follow-up questions, will be audio-recorded, transcribed verbatim, and coded according to phenomenological methodology. Results will be presented in future articles; this protocol will therefore not cover this in-depth.

### Statistical analyses

#### Sample size

Based on previous studies examining ACL-RSI [49] and side-hop function [50], a preliminary sample size was estimated, to be used in the first phase of this adaptive RCT, which resulted in *n*=106 participants. This included adjustments for potential cluster effects using a preliminary Intra-Cluster Correlation Coefficient (ICC). An approximation is required as comparable studies are unavailable to reliably perform a sample size estimation. This is necessary in this phase in order to evaluate whether an intervention effect is detectable and within practical limitations, which will thereafter inform more accurate sample-size estimations.

A new sample size will be calculated by a blinded third-party member of the data management committee using collected data from an interim analysis, therefore allowing for more accurate between-group differences in the main outcomes. Observed within- and between-cluster variance will also be calculated in order to more accurately estimate an Intra-Cluster Correlation Coefficient (ICC, denoted as *ρ*). This will be performed using the formula $$ \rho =\frac{s_b^2}{s_b^2+{s}_w^2} $$ [51] in order to adjust for the fact that different clinics are included in the trial (i.e., potential clustering effects). The adjusted sample size will therefore be calculated using the formula $$ \frac{n_ik\left(1-\rho \right)}{k-{n}_i\rho } $$ [52], along with an estimated 20% drop-out rate, in order to reach a power of 0.80, with significance set at *p*<0.025. As an estimated sample size has been calculated, the new sample size will only be adjusted up; that is, the number of participants included will not be less than *n*=106 required in the original sample-size estimation.

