## Methods

### Study design

The design of this study is a 1:1 single assessor-blinded cumulative adaptive cluster-randomized controlled trial, conforming to the Consolidated Standards of Reporting Trials (CONSORT) statement extension for pragmatic trials [25], with the intervention administered in real-world settings and conditions (trial pragmatism illustrated in Additional File 1). The cumulative adaptive design allows for modification upon evaluation of a subgroup in order to more accurately determine the required sample size, as well as whether changes need to be made to the method before the continuation of the trial [26]. Items from the World Health Organization Trial Registration Data Set are available on the ClinicalTrials.gov registration page (NCT03473821). This protocol adheres to the Standard Protocol Items: Recommendations for Interventional Trials (SPIRIT) guidelines [27], procedures of which are outlined in Fig. 1 (SPIRIT checklist available as Additional File 2). Ethical approval has been granted by the Regional Ethical Review Board in Lund, Sweden (Dnr 2016/413, Dnr 2018/927).

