#### Adaptive design modification criteria

The mean scores of the main outcomes (side hop and ACL-RSI) will be compared in exploratory interim analyses once *n*=25 participants have been included in both groups. Analyses will be performed by a blinded third-party data management committee (DMC) and blinded to treatment arms until after an initial data analysis and interpretation. The purpose of the interim analysis is primarily to gain data with which a more reliable sample size can be calculated based on observed differences, as well as to identify potential benefits and harms which may thereby determine whether modifications are required. Therefore, differences in the main outcomes from baseline to 12 weeks will be compared using estimations from the previously defined clinically relevant differences as modification criteria, as both groups are expected to improve. Continuation without modification will be allowed if the between-groups difference in ACL-RSI is ≥5 points, and/or muscle function (LSI) in the side-hop test is ≥8 in favor of the MOTIFS group, each analyzed separately. These estimates correspond to a small to medium effect size (Cohen’s *d*≈0.1–0.3) based on previously defined clinically relevant values and will be used to determine the potential for the MOTIFS model to exhibit an effect. However, as previous studies which provide enough data for reliable calculation are lacking, these effect sizes are theoretical estimations which require further data to confirm. The estimates take into account the small sample size in the interim analysis and serve as a guide to whether the differences exhibit a trend indicating acceptable power upon completion of data collection, without unnecessarily prematurely ending the trial. If these initial criteria are not met, difference in enjoyment (PACES) scores of approximately 5 points will be deemed acceptable, estimated based on studies examining the effect of enjoyment on physical activity adherence in uninjured people [53]. Increased adherence to rehabilitation training will likely lead to improved rehabilitation outcomes based on a dose-response relationship, so increased enjoyment is considered an acceptable criterion for the continuation of the trial. Upon completing the interim analysis, the DMC will determine whether these criteria are met, and/or whether modifications are necessary, and a new sample size calculation will be performed.

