Modification recommendations will be made based on observed data to identify potential harms or an unrealistic new estimated sample size estimation (i.e., more than 100 patients in each group), for example. In this case, the method will be refined to ensure that the model’s efficacy is maximized according to the proposed outcomes (i.e., psychological readiness to return to sport and muscle function results) and that implementation is clinically relevant and feasible for the end-users. Pilot testing will then be performed again, examining a new pilot population a maximum of one additional time to evaluate whether a satisfactory level of clinically relevant power is achieved (i.e., continuation criteria are met), thereby justifying the continuation of the trial. Modifications will be informed by preliminary results from interim analyses of this cumulative adaptive trial examining both participant data and PT interview responses in the research team, DMC, and potentially discussions with a focus group comprised of end-users (PTs and patients). Following the initial interim analysis, the *p* value will be adjusted using a Bonferroni correction to take into account the risk of type-I error inherent in repeating the pilot phase.

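### The new sample size is to be calculated from the between-group difference seen in about 25 people per arm, which is too imprecise to assure the stated 0.80 power

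*Protocol article*

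**What the plan says.** Under Sample size, the protocol article describes 106 as a first estimate: "a preliminary sample size was estimated, to be used in the first phase of this adaptive RCT". It then says that a new n will be calculated "using collected data from an interim analysis, therefore allowing for more accurate between-group differences in the main outcomes", with an ICC estimated from the same interim data, "along with an estimated 20% drop-out rate", "in order to reach a power of 0.80, with significance set at *p*<0.025". The new n may rise above 106 but not fall below it.

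Under Adaptive design modification criteria, the interim takes place once 25 participants have been included in both groups. Its purpose is "primarily to gain data with which a more reliable sample size can be calculated based on observed differences". The clinically relevant differences (5 points on ACL-RSI, 8 on side-hop LSI, described as d of about 0.1 to 0.3) serve as criteria for continuing without modification. They are not named as the target of the recalculation. A new n above 100 per group is given as an example of a ground for recommending modification, after which the method is refined and the pilot repeated at most once. The section ends by saying that, after the initial interim, the p "value will be adjusted using a Bonferroni correction to take into account the risk of type-I error inherent in repeating the pilot phase".

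**The concern.** A sample size should rest on the difference the trial needs to detect. Here it rests on the difference that a small interim happens to show. The required n varies with the inverse square of that difference, so its error is strongly magnified. A favourable interim leaves the trial at 106 when more people are needed. An unfavourable one yields an n that the plan calls unrealistic, and the plan's response is to refine the intervention, which cannot correct sampling error, a large SD or a large ICC.

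The alpha is a second, separate point. The recalculation uses 0.025, while a later paragraph announces a further correction without saying how it relates to that figure. If the final test is stricter than the one the trial was sized for, power is lost.

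**Working it through.** **Inputs from the article.** 106 in total, 53 per arm; power 0.80; alpha 0.025; drop-out 20%; interim at 25 per arm; floor of 106; more than 100 per arm as an example ground for modification.

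**Assumptions, because the article does not give the figures.** One outcome, known SD (set to 1), no clustering, two-sided test, true d of 0.3, 0.5 or 0.67.

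**The plan's own figure.** The 106 cannot be reproduced, because the article does not give the difference, SD, ICC or number of clinics. Solved backwards without clustering, 53 × 0.8 = 42.4 evaluable per arm gives d = (2.241 + 0.842) × sqrt(2/42.4) = 0.67. This is why 0.67 is used as the favourable case.

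**Precision of the observed difference.** SE = sqrt(2/25) = 0.28, a 95% half-width of 0.55. With 20 per arm left after drop-out it is 0.32. If the 25 means both groups together, it is 0.40.

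**Calculated n per arm.** n = 2 × (2.241 + 0.842)² / d² / 0.8 = 23.76 / d². The true requirement is about 264 at d=0.3, 95 at d=0.5 and 53 at d=0.67.

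- n exceeds 100 when the observed d is below sqrt(23.76/100) = 0.487, which includes every wrong-sign result.
- n is at or below the floor of 53 when the observed d is at least sqrt(23.76/53) = 0.670.

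The observed d is normal around the true d with SE 0.283. For example, at d=0.5 the chance of exceeding 100 is Φ((0.487 − 0.5)/0.283) = 0.48.

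| True d | Above 100 or wrong sign | Wrong sign alone | Left at floor | Median n (quartiles) before floor, positive differences |
|---|---|---|---|---|
| 0.3 | 75% | 14% | 10% | 191 (86–605) |
| 0.5 | 48% | 4% | 28% | 89 (48–211) |
| 0.67 | 26% | 1% | 50% | 52 (31–100) |

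**Power with n held to 53–100 per arm.** Power = Φ(d × sqrt(m/2) − 2.241), where m = 0.8n is the evaluable number per arm.

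| True d | At 53 per arm | At 100 per arm | Average over interims |
|---|---|---|---|
| 0.3 | 19% | 37% | 34% |
| 0.5 | 52% | 82% | 70% |
| 0.67 | 80% | 98% | 87% |

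The averages treat the final test as independent of the interim result. If the interim participants are kept in the final analysis, as a cumulative design suggests, simulation gives 35%, 78% and 95%. If n may rise to 1,000 per arm, the same simulation gives 80% at d=0.3 and 91% at d=0.5.

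**ICC.** The approximate SE of an ICC from k clinics of m people is (1−ρ)(1+(m−1)ρ) × sqrt(2/(m(m−1)(k−1))). Assuming ρ = 0.05 and 10 clinics of 5, this is 0.95 × 1.2 × sqrt(2/180) = 0.12. Spreading 50 people over 4 to 20 clinics gives about 0.10 to 0.17. The error is at least twice the assumed value throughout.

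**Alpha.** Assuming the Bonferroni step divides 0.025 by 2, the critical value rises from 2.241 to 2.498. Power becomes Φ(3.083 − 2.498) = 72%. Restoring 80% needs ((2.498 + 0.842)/3.083)² = 1.17 times as many people, so 106 becomes about 125. With one-sided tests, power is 71%.

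**The case against.** Four stronger readings are tempting, and the documents do not support them.

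- A reader might infer that the trial's size becomes almost random. The new n cannot fall below 106, and more than 100 per group prompts review before anyone is enrolled to that number. The wide spread belongs to the calculated n, not to recruitment.
- A reader might infer that 80% power is lost in every case. It is not: at d near 0.67 average power stays above 80%, and with n free to rise and interim participants retained it is about 80% or more at alpha 0.025. The shortfall arises at small to moderate effects when n is held to 100 per arm.
- A reader might take 48% as the chance that a useful treatment is sent back. The article never states d=0.5, and at that value the true n is about 95, so a limit of 100 is bound to be crossed about half the time. At d=0.3 the limit is crossed mostly because the true n really is above it. Continuation also has its own criteria: ACL-RSI and/or side hop, with PACES as a fallback, and the data management committee decides. With true d=0.5 on both outcomes and thresholds at d of 0.1 to 0.3, at least one main criterion would be met in about 89–99% of interims (outcome correlation 0 to 0.5).
- A reader might infer that the final test will certainly be stricter than the one sized for. The Bonferroni sentence opens as a step after the initial interim but gives repeating the pilot as its reason. It may apply only on that path, or 0.025 may already contain it.

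It is also fair that a near-zero interim ICC cannot remove the inflation already in the 106. It can remove it only from an increase above 106. What survives is that the article explicitly makes the observed difference the basis for the new n. It also admits that the planning values are theoretical, which supports re-estimating variance and ICC but not letting a noisy estimate replace a relevant difference.

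**Conclusion.** The point holds in this limited form and should be corrected. The recalculated n rests on a difference with SE of about 0.28 SD, before clustering and drop-out add to it, so 0.80 power is not assured. With n held to 53–100 per arm, power falls well short at d=0.3 (34–35%). It falls short at d=0.5 by 2 to 10 points, depending on whether interim participants count in the final test. It does not fall short at d=0.67. These figures assume one outcome, known SD, no clustering and two-sided 0.025; an ICC estimated from about 50 people adds further noise.

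The alpha point is conditional. The cost is 8 points of power, or 17% more people, only if the correction applies on top of 0.025 with a divisor of 2. What is certain is that the two passages do not say how they fit together.

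**What to change.** Change the recalculation wording as follows:

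1. Hold the target difference for each main outcome at a pre-specified relevant value, and state that value.
2. Re-estimate only SD, ICC and drop-out at the interim, and do not let the ICC fall below the planning ICC.
3. State when the Bonferroni step applies and its divisor, and calculate n at the alpha that will finally be tested.
4. If n exceeds 100 per arm because of SD or ICC, restate the detectable effect or the power. Do not treat it as evidence that the intervention needs refining.

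The cost is a wording change before the interim. The article reports 35 participants included at the time of writing, so on the 25-per-arm reading the interim had not then been reached. The downside is that n no longer reacts to the observed effect and may come out larger. With a target of d=0.3, for example, it would be about 264 per arm (about 530 in total) before cluster inflation.

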**Methods:**

This pragmatic 1:1 single assessor-blinded adaptive cumulative cluster-randomized controlled trial will include 106 knee-injured people with a goal of returning to physical activity. Participants are randomized to either the MOTIFS or Care-as-Usual condition. Primary outcomes are the ACL Return to Sport after Injury Scale and change in injured leg hop performance in a side hop task from baseline to 12 weeks. Secondary outcomes include patient-reported outcomes and assessment of muscle function using a hop test battery and Postural Orientation Errors at 12-week follow-up. At 12-month follow-up, patient-reported outcomes are assessed. A sub-group (7-10 in each group) will be interviewed to gain insight into experiences of rehabilitation.

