Shifting the focus to individual relevance may influence motor learning and performance of experienced-based movements, according to the OPTIMAL theory of motor learning [21]. This is also supported by the theory of re-investment, which states that motor execution can be disrupted through attempts at conscious control [22]. For example, focusing on how to execute a situation-based (i.e., soccer) task, rather than on movement technique, relies more on automatic processes to create efficient movement [22]. A more external focus also creates an understanding of the applicability of the movement, shifting motivation from extrinsic (outcome-oriented) to intrinsic (inherent satisfaction), which is important for adherence [23]. Adherence may then also influence physical outcomes by virtue of having performed the exercises [24].

Integrating DMI into knee-injury rehabilitation constitutes a potential alternative to improve the effectiveness of rehabilitation by targeting a gap in the rehabilitation literature. This allows for specific interventions that can be used in a clinical environment which aim to address and affect physical, neurological, and psychological aspects.

This study protocol describes an ongoing adaptive randomized controlled trial, the aim of which is to compare the efficacy of rehabilitation with integrated dynamic motor imagery, and rehabilitation alone (care-as-usual) in terms of improving both muscle function and patient-reported outcomes in physically active males and females with a traumatic knee injury and with a goal of returning to physical activity. This approach of integrating physical and psychological aspects in rehabilitation takes a holistic perspective of the injury, in contrast to an isolated physical perspective in care-as-usual rehabilitation.

The main hypothesis is that 12 weeks of rehabilitation with integrated dynamic motor imagery will improve patient-reported psychological readiness to return to physical activity and objective muscle function to a greater extent than CaU rehabilitation.

Secondary aims include examining the effect of rehabilitation with integrated DMI on patient-reported outcomes, performance in a hop battery, and postural orientation. The exploratory aims include a phenomenological interview with patients to gain further insight into the perceived experiences throughout the rehabilitation process.

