#### Main outcomes

This trial includes two main outcomes. Psychological readiness to return to sport is evaluated using the Swedish version of the ACL-Return to Sport after Injury scale (ACL-RSI), which includes an emotional response, confidence, and risk-appraisal when returning to sport after an ACL injury [33, 34]. Physical function is evaluated using the change in number of hops in the injured leg from baseline to 12 weeks for the side hop task.

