#### Data analysis

The analysis will be done using the IBM SPSS statistical software package (IBM Corp., Armonk, New York, USA). Primary analyses of the entire sample will be done according to intention-to-treat principles. A dose-response analysis will be performed to determine effective adherence. Per-protocol analyses will be performed for those participants with at least 70% adherence (corresponding to two trainings per week), as a preliminary estimate of the effective number of training occasions. This is in order to eliminate cross-over and drop-out effects in the total sample, as well as to evaluate the training for those that have reached a pre-defined level of adherence deemed acceptable to have an effect. Sensitivity analyses will be performed to determine whether within-cluster correlations indicate potential effects due to being clustered, for example, by the clinic or by PT. Patient cross-over (i.e., patients changing clinics) is a low-risk possibility and will be recorded in case of occurrence. All outcome variables will be examined for normality using appropriate testing (e.g., Kolmogorov-Smirnov). Complete-case analyses are the primary analyses, and sensitivity analyses will be done depending on the number of missing values. Missing values are not expected to be extensive, and if less than 5% of data is missing, the whole data set will be analyzed along with a sensitivity analysis with appropriate imputed values. If between 5 and 40% of data is missing, appropriate multiple imputation methods will be used, which will be informed by blindly assessing results of the interim analysis, and a complete-case analysis will be done with appropriate sensitivity analyses. If over 40% is missing, a complete case analysis will be done with no sensitivity analysis.

Results will be analyzed using independent samples *t* tests to examine between-group differences of the change from baseline to a 12-week follow-up. Where appropriate, equivalent non-parametric Wilcoxon signed-rank testing will be used to compare between-group differences. The main analysis will focus on the two main outcomes, with secondary outcomes acting as support for these. Secondary outcomes therefore carry less weight and issues with potential error due to the number of evaluations will be discussed when results are presented.

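### If p<0.025 is 0.05 split between the two main outcomes, a Holm step-down keeps the same familywise error and lifts each outcome's power from 80% to about 85% when both effects are real

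*Protocol article*

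**What the plan says.** Under Main outcomes, the protocol article states: "This trial includes two main outcomes". They are ACL-RSI and the change in number of side hops on the injured leg from baseline to 12 weeks. The Data analysis section treats them together: "The main analysis will focus on the two main outcomes, with secondary outcomes acting as support for these". It compares the arms by t tests on change and gives neither a significance level nor an order of testing.

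The only significance level for these outcomes is in the Sample size section, where the sample size is to be recalculated "in order to reach a power of 0.80, with significance set at" p<0.025. No reason for 0.025 is given.

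One other multiplicity statement exists. Adaptive design modification criteria adds a Bonferroni correction, after the first interim analysis, for the type I error risk of repeating the pilot phase, which may happen at most once more. The size of that correction is not stated.

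**The concern.** Two outcomes and a level of 0.025 suggest 0.05 divided equally. A fixed equal split holds the second outcome to 0.025 even after the first has been shown, although by then that outcome's share of alpha can be reused without breaking the familywise limit. Holm reuses it.

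What is at stake is power on the claim the trial most wants to make. The main hypothesis is that the intervention "will improve patient-reported psychological readiness to return to physical activity and objective muscle function to a greater extent than CaU rehabilitation", which joins the two outcomes. Suppose ACL-RSI is clearly positive and the side hop gives p = 0.035. With an overall alpha of 0.05, the fixed split leaves physical function not shown, while Holm shows it under the same familywise limit.

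**Working it through.** **Inputs.** From the protocol article: two main outcomes; power 0.80; level 0.025; 106 participants, 1:1; 20% drop-out. Assumed, because the article does not give them: 0.025 is 0.05/2; tests are two-sided; the two test statistics are bivariate normal with correlation 0 to 0.9; each test has its nominal error rate.

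**The plan's own figure.** The 106 cannot be rebuilt, because the effect size, SD, ICC and cluster size behind it are not given. Ignoring clustering, the detectable standardised difference is 3.083 × √(2/n per arm). That is 0.60 with 53 per arm, and 0.67 with 42.4 per arm (106 less 20%, halved). The 80% baseline is therefore taken as the protocol's target, not as a verified figure.

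**Familywise error.** Fixed split: 0.025 + 0.025 = 0.05 at most; 1 − 0.975² = 0.0494 if independent. Holm with overall alpha:
- If both nulls are true, an error needs the smaller p below alpha/2, which has probability at most alpha/2 + alpha/2 = alpha.
- If one null is true, an error needs that p below alpha, which has probability at most alpha.

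Both bounds hold under any correlation. Simulation with 2 million draws at alpha 0.05 gave 0.0495 (correlation 0) and 0.046 (0.5) with both nulls true, and 0.045 and 0.042 with one true null.

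**Power per outcome.** The mean of each test statistic giving 80% power at two-sided 0.025 is 2.241 + 0.842 = 3.083. Power at two-sided 0.05 is then Φ(3.083 − 1.960) = 0.869. Under Holm an outcome is shown if its own p is below 0.025, or if it lies between 0.025 and 0.05 and the other p is below 0.025. With independence:

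0.80 + 0.80 × (0.869 − 0.80) = 0.855.

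**Power to show both**, with independence: fixed 0.80² = 0.640; Holm 2 × 0.80 × 0.869 − 0.640 = 0.751.

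Bivariate normal results, in per cent:

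| Correlation | Each, fixed | Each, Holm | Both, fixed | Both, Holm |
|---|---|---|---|---|
| 0 | 80.0 | 85.5 | 64.0 | 75.1 |
| 0.3 | 80.0 | 85.0 | 66.6 | 76.6 |
| 0.5 | 80.0 | 84.6 | 68.7 | 77.8 |
| 0.9 | 80.0 | 83.2 | 75.0 | 81.5 |

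Simulation gives 85.6% rather than 85.5% at correlation 0. The chance of showing at least one outcome is the same under both rules (96.0% at correlation 0, 91.3% at 0.5). If the tests were one-sided with 0.05 split in two, Holm gives 86.1% and 85.0% per outcome at correlation 0 and 0.5.

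**When the effects are unequal** (independence; one outcome at design size):
- Other outcome has no effect: 0.80 + 0.025 × 0.069 = 0.802.
- Other outcome has half the design effect (power 0.242 at 0.025): 0.80 + 0.242 × 0.069 = 0.817.
- Other outcome has 70% of the design effect: that weaker outcome's own power rises from 46.7% to 55.6%.

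**The pilot-repeat correction.** If it halves overall alpha to 0.025, Holm must run at 0.0125 and then 0.025. Running it at 0.025 and then 0.05 would allow a familywise error of up to 0.05, twice the intended limit.

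**The case against.** The strongest reply is that nothing in the document is wrong: an equal Bonferroni split is valid, and a testing order may sit in a statistical analysis plan that is not shown. The first half stands. A reader might infer that error control fails or that the analysis section binds each outcome to 0.025; neither is supported. The level appears only in the sample-size text, and the absence of a step-down rule is not itself a defect. What remains is that the one level the article fixes for its two main outcomes, read as a split, can be improved on at the same familywise error.

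A second reply is that 0.025 could have another origin. One repeat of the pilot makes two occasions, and 0.05/2 is again 0.025. The article does not settle this. On that reading the other 0.025 is reserved for the repeat and cannot pass between outcomes. This stands, and it is why the recommendation is conditional and written in terms of the remaining overall alpha. Equally, if success required both outcomes, no split would be needed and the argument would change.

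Third, a reader might infer that the gain to 85% is assured and free. It is not assured: it needs both effects at design size, and the article itself calls its planning values theoretical. Nor is it wholly free. A fixed split has directly matching 97.5% intervals, which Holm lacks in simple form. The error rate on a true null also rises from 0.025 to about 0.042-0.045 when the other effect is real, still within the familywise limit.

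**Conclusion.** The point holds as a conditional, minor improvement. If 0.025 is 0.05 shared between the two main outcomes, Holm gives the same familywise protection and never rejects less. With both effects at the design size, power per outcome rises by about 5 percentage points. Power to show both rises by about 9 points (correlation 0.5) to 11 points (correlation 0). With no effect on the other outcome the gain is about 0.2 points.

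This rests on the inferred meaning of 0.025, on a claim being possible for either outcome alone, on the unverified 80% baseline, and on correlations that the article does not give. It does not support calling the present level wrong, nor writing 0.025 and 0.05 into the plan without regard to the pilot-repeat correction.

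**What to change.** In the analysis section, state that 0.025 is the two-outcome split, if it is, and what overall alpha remains after the pilot-repeat correction. Then specify Holm within that alpha: the smaller of the two p values is tested against alpha/2 and, only if it is significant, the larger against alpha. That means 0.025 then 0.05 if alpha is 0.05, and 0.0125 then 0.025 if the correction halves it. Keep alpha/2 as the conservative planning level for the sample size.

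The rule should be fixed before anyone sees unblinded results. When the article was written, 35 participants had been included, short of the 25 per group that triggers the interim analysis.

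The cost is one or two sentences, with no added participants, data or familywise error. The small downside is interval reporting: the plan should say which confidence intervals will accompany the Holm decisions.
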